## Statistical analyses

### Effectiveness analyses

Analyses will be based on an intention-to-treat principle by including all randomized participants into the analyses. Primary and secondary outcomes will be analysed using a linear mixed model, assuming data are missing at random. The mixed model for the primary outcome (depression) will include group, time (all three points of assessment) and the interaction of group and time as fixed effects and recruiting outpatient clinic as random effect. Secondary outcomes will be analysed accordingly. We will calculate between-group effect sizes for the primary outcome using the post-treatment depression means and their pooled observed standard deviation. Additional per protocol analyses will include only those participants who have not started psychotherapy until the end of all study procedures, completing all three assessments, and, regarding the intervention group, at least five intervention modules.

We will evaluate the clinical relevance of any given development in a generalized linear model by estimating numbers of treatment response and deterioration (based on the reliable change index; [71]) and symptom remission (ADS-L score < 22; [41]), and by calculating the number needed to treat (NNT) for one more remitted participant.

Potential moderators influencing treatment effects will be analysed in the mixed model analysis. As there is at this point little research concerning moderating variables in the field [72], these analyses follow an exploratory approach. Potential influencing variables include socio-demographics, internet affinity or attitudes towards psychotherapy.

Analyses will be performed using an alpha level of .05 and two-sided tests. All analyses will be conducted using IBM SPSS.

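### The between-group d ignores T1 and leaves the source of its means open, and the missing-data provision does not reach the response, remission and NNT analysis

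*Protocol article*

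**What the plan says.** All of the relevant text is in the protocol article, Statistical analyses, Effectiveness analyses.

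- Population: "Analyses will be based on an intention-to-treat principle by including all randomized participants into the analyses".
- Missing data: "Primary and secondary outcomes will be analysed using a linear mixed model, assuming data are missing at random". The model terms listed are group, time and their interaction as fixed effects, and outpatient clinic as a random effect.
- Effect size: calculated "using the post-treatment depression means and their pooled observed standard deviation".
- Clinical relevance: "We will evaluate the clinical relevance of any given development in a generalized linear model by estimating numbers of treatment response and deterioration", together with remission, and "by calculating the number needed to treat (NNT) for one more remitted participant". No handling of a missing score and no NNT denominator is given here.
- Restriction to complete assessments: stated only for the supplementary analysis, where "Additional per protocol analyses will include only those participants who have not started psychotherapy until the end of all study procedures, completing all three assessments".

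Two other sections bear on the point. Proposed sample size plans on the between-arm difference in pre-to-post change. Inclusion and exclusion criteria make a completed baseline a condition of entry, so T1 should be available for everyone randomized.

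**The concern.** The plan sets one population rule and then names three kinds of result: the mixed-model test, a standardized difference d, and counts of response, deterioration and remission with an NNT. The missing-at-random provision belongs to the first. A generalized linear model with no random effect and no imputation drops every participant whose outcome score is missing. A d built from post-treatment means is an observed-case figure unless the means come from a model that carries information from T1 to T2.

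Readers will quote d and the NNT. If these rest on T2 responders only, they describe a different set of people from the primary test and need a stronger assumption about dropout. Unequal dropout is plausible because only one arm has modules to work through before T2. The Discussion acknowledges considerable dropout in web-based interventions, although stopping the modules is not the same as missing the T2 assessment.

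**Working it through.** **The plan's own figure.** For d = 0.56, two-sided alpha 0.05 and 90% power, n per arm = 2 × (1.960 + 1.282)² / 0.56² = 67.0, rounded up to 68. The exact t-test power at 68 per arm is 0.900. The stated 68 per arm reproduces and is not in dispute.

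**Inputs for the illustration.** The article gives no dropout rate after randomization, no T1-T2 correlation (rho) and no remission rate. All of these are assumptions below. Scores are in SD units and negative values favour the intervention.

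**Effect of observed means on d.** Let T2 have correlation rho with T1, and let missingness depend on T1 only. The observed-mean difference is then the true difference plus rho × (mean T1 of responders in the intervention arm minus that in the control arm). In large-sample simulation with true d = -0.50 and, where missingness depends on severity, a log-odds slope of 0.8 per SD of T1:

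| rho | Missing T2, intervention / control | Depends on severity in | Observed-mean difference |
|---|---|---|---|
| 0.6 | 31% / 13% | intervention arm only | -0.63 |
| 0.6 | 31% / 16% | both arms | -0.56 |
| 0.3 | 31% / 16% | both arms | -0.53 |
| 0.6 | 21% / 21% | both arms | -0.50 |
| 0.6 | 29% / 13% | neither arm | -0.50 |

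The first two rows are -0.633 and -0.563 before rounding. Their biases are 0.133 / 0.50 = 27% and 0.063 / 0.50 = 13%. By the formula they imply T1 gaps between responders of 0.133 / 0.6 = 0.22 SD and 0.063 / 0.6 = 0.105 SD. Regression on T1 returned -0.50 in every row. Dividing by the observed SD (0.985 to 1.00 here) moves these figures by at most about 0.01.

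**A second set of assumptions.** True d was 0.56 in size, rho 0.4 or 0.6, dropout 10% to 40%, and the severity slope 0.7. Observed means gave 0.56 to 0.57 when rate and severity dependence matched across arms, and 0.59 to 0.72 otherwise. Baseline-regression means over the observed SD gave 0.56 to 0.57 throughout.

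**Which model the means come from.** In a simulation of the first row with 6,000 per arm, observed means gave -0.634. A mixed model with only a clinic random effect gave -0.635. A model with a participant random intercept gave -0.503. The terms listed in the article include no within-person correlation. Model-estimated means recover the true value here only if that correlation is modelled.

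**NNT.** In the second set, remission rates of about 37% and 18% give a true NNT of about 5.5. Observed cases gave 4.2 to 5.4. Counting missing as not remitted gave 5.6 to 11.8. Even with matched dropout the observed-case NNT was slightly low, at 5.1 to 5.4. With 20% missing, an observed-case analysis keeps 0.8 × 136, or about 109 participants.

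**Precision, apart from dropout.** At 68 per arm with complete data, the standard error of an unadjusted d is about √(2/68) = 0.17. Adjusting for T1 with rho = 0.6 multiplies it by √(1 - 0.36) = 0.8, giving 0.14.

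**The case against.** The strongest reply is that the article never says what a suspicious reader might infer. Only the SD is called observed, and the sentence follows directly on the mixed model. Naming an observed SD makes good sense if the means are model-estimated, and that is a legitimate standardization. The population rule opens the section and covers everything after it. A generalized linear model fitted to imputed data would satisfy it, and imputation detail is commonly left to an analysis plan that is not shown. This stands. The text does not support the reading that the plan uses raw means, or that it restricts the binary analyses to observed cases.

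It also stands that d and the NNT are supplementary, since inference on the primary outcome rests on the mixed model. The size of any bias depends on chosen inputs, and it vanishes for d in the last two rows of the table.

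The reply does not settle the matter. The article does fix an estimator for d, a model for the binary outcomes, a population and a missing-data assumption, and the last is tied to a different model. As worded, d uses no baseline information, although the sample size rests on change from baseline. Reading the means as model-estimated helps only if the model carries a within-person term, which the listed terms do not include.

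**Conclusion.** The point holds as a weakness in stated methods, not as a demonstrated contradiction. The d makes no stated use of T1, and its means may be raw or model-estimated. The missing-at-random provision does not extend to the generalized linear model behind response, deterioration, remission and the NNT. Applied to observed scores, both can depart from the rule that all randomized participants are analysed.

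A reader might conclude that the reported d will be exaggerated by 27%. The documents do not support that. The figure needs severity-dependent dropout in one arm only, at more than twice the other arm's rate, and rho = 0.6. A fair summary is -0.56 to -0.63 against a true -0.50 in the two unfavourable scenarios with rho = 0.6, and no bias in d if dropout is equal across arms or unrelated to severity. The NNT is more sensitive. Under the assumed inputs it runs from 4.2 to 11.8 around a true value of about 5.5, depending on the dropout pattern and on which missing-data rule is used. The precision gain from using T1 does not depend on any dropout pattern, only on rho.

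The primary test is not undermined by this point. The change is worth making before analysis.

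**What to change.** 1. **Effect size.** Define d as the model-estimated, baseline-adjusted T2 difference, from a model that includes within-person correlation, divided by the pooled observed post-treatment SD already named. Report it with a CI. A pooled T1 SD would be a poor substitute, because participants are selected on the same scale (CES-D > 22). If 65% pass the cut-off and screening correlates 0.7 to 0.9 with T1 (assumed), the T1 SD is 0.86 to 0.75 against a T2 SD of 0.95 to 0.92. The T1 SD would then enlarge d by about 11% to 23% (0.95/0.86 to 0.92/0.75).
2. **Binary outcomes.** Multiply impute the CES-D total by arm, using T1, T2, T3 and clinic. Derive response, deterioration and remission in each data set, fit the generalized linear model and pool the results.
3. **NNT.** Report it with its CI and state that the denominator is all randomized participants.

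The cost is a few sentences in the plan and a small amount of extra analysis work, with no new data collection.

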### Proposed sample size

The sample size calculation is based on the difference in change in the primary outcome (depressive symptoms) from pre- to post-treatment in both treatment arms (intention-to-treat analysis). Considering recent meta-analytic effect sizes for web-based depression interventions, an effect size of *d* = 0.56 [33] can be expected and is considered feasible for the type of intervention (guided intervention, naturalistic study design, cf. [44]). On the basis of a two-sample t-test at a two-sided significance level of .05, the study is planned to detect this effect with 90% power. This requires a sample of 68 individuals in each arm.

With a target sample size of *N* = 136 for randomization, at least 597 screeners have to be sent out. Based on previous research, it is expected that about 50% of the contacted people are interested in study participation [37]. Further, about 65% of those interested are expected to score above the cut-off for depressive symptoms [45], resulting in 194 potential participants. A 30% loss is expected due to incomplete baseline, suicidal ideation or missing informed consent, leaving 136 participants for randomization.

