##### Current Psychotherapy

At all points of assessment participants indicate their current motivation and their perceived need for psychotherapy, and whether they are currently receiving face-to-face psychotherapy. Participants indicating their current receipt of psychotherapy are asked how many sessions they have had and when their first appointment has been. Participants not receiving face-to-face psychotherapy are asked to indicate reasons.

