This study also has a few limitations which deserve note. As the study will be conducted in the context of routine mental health care, the waiting periods of participants will vary depending on the capacities of the cooperating outpatient clinics. Some participants will presumably start psychotherapy between post- and follow-up assessments. However, due to the limited time span between post and follow-up assessments, the take-up of a subsequent psychotherapy cannot be reliably assessed. Per protocol analyses will be conducted including only those participants who have not started psychotherapy until the completion of follow-up assessments. Due to the routine care setting and in favor of external validity, we include participants who may suffer from other primary psychological symptoms (e.g. anxiety). These participants might benefit more from other disorder-specific interventions. Nonetheless, trials have implemented web-based depression interventions in routine care settings with high external validity and put forth large effect sizes (e.g. [36, 37]). Similar effects are expected in this study as all participants suffer from depressive symptoms and take an informed choice to partake in an intervention for mood improvement.

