When it comes to web-based interventions, considerable dropout rates have been reported [76]. The participants dropping out of the intervention will be asked for their reasons to do so, thus dropouts will be used for a deeper understanding of intervention acceptance and applicability. In an attempt to minimize intervention dropouts, we implement a web-based intervention with guidance [19]. Additionally, per protocol analysis will be performed for a high quality data analysis. Another limitation is that the main outcome data is based on self-reports. This is a frequently conducted approach with a favorable study cost–validity balance, still clinician-rated outcome measures would be beneficial. We have selected measures with high internal consistency and validity. In line with other research in the field (e.g., [63, 77]), retest-reliabilities are not reported as studies vary greatly in terms of evaluation times and sample characteristics, which makes retest-reliabilities difficult to interpret in the context of this study design. Also, due to related effort, no analyses of cost-effectiveness are performed in this study. Last, the recruitment of participants has started in February 2017; however, the study has been registered before the beginning of recruitment and no changes have been made to the registry.

The results of this study will be of great relevance for daily clinical practice, as they reflect the applicability of an evidence-based self-help treatment option for individuals seeking psychotherapeutic treatment. Addressing the problem of prolonged waiting periods, it is essential to investigate which treatment options are effective and accepted by those in need. Evidence-based interventions with minimal effort for outpatient clinics are scarce and urgently needed. Thus, implementing a web-based intervention in this setting may be beneficial for those on a waitlist and health care providers. Also, this study investigates a model to viably integrate web-based interventions into the health care system. Considering the growing interest and realization of new treatment approaches, such as stepped-care models [78, 79], web-based interventions have the potential to play an important role as low-intensity interventions in the treatment of depression [80]. As Kazdin and Blase [81] emphasize, innovative treatment approaches are needed to decrease the burden of mental diseases on a large scale.

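### The single per-protocol set makes the T2 comparison depend on events after T2 and selects on module completion in one arm only, so its bias has no known direction

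*Protocol article*

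**What the plan says.** The main analysis is by intention to treat on all randomised participants, with a linear mixed model over T1, T2 and T3. The per-protocol analyses are described as additional. They keep "only those participants who have not started psychotherapy until the end of all study procedures, completing all three assessments". A further condition applies in one arm alone: "regarding the intervention group, at least five intervention modules". The Discussion repeats the psychotherapy condition, again running to the completion of follow-up. No separate set is given for T2.

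Four other statements bear on this rule:

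- Discussion: "Some participants will presumably start psychotherapy between post- and follow-up assessments".
- Discussion, after the remarks on dropout: "per protocol analysis will be performed for a high quality data analysis".
- Current Psychotherapy: at every assessment, participants in psychotherapy are "asked how many sessions they have had and when their first appointment has been".
- Control condition: controls reach the web-based intervention only after follow-up.

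The sample size rests on the change from pre- to post-treatment, and the between-group effect size is to be computed at post-treatment. T2 is therefore the time point that carries the trial.

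**The concern.** There are two separate problems.

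**Conditioning on the future.** T2 is seven weeks after randomisation. Whether a T2 score enters the per-protocol comparison depends on what happens after it was recorded: a psychotherapy start between T2 and T3, or a missed T3. Neither event can have contaminated the T2 score, but either may be related to how the participant felt at T2. The rule discards usable data and may select on the outcome.

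**Selection in one arm.** Intervention participants must have completed at least five of six modules. Controls cannot be filtered in the same way. People who chose to persist are compared with controls of whom persistence was never asked. The protocol itself, under Acceptance analyses, lists depressive symptoms and former psychotherapy as possible predictors of adherence, so a link between adherence and prognosis is not far-fetched.

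At stake is the reading of the per-protocol result. The protocol presents it as the response to psychotherapy starts and, beside the remarks on dropout, as a gain in data quality. It gives up randomised comparability, and no adjustment for that is stated.

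**Working it through.** **1. The plan's own figure.** The inputs are in Proposed sample size: "an effect size of *d* = 0.56 [33] can be expected", two-sided alpha 0.05, 90% power. n per arm = 2(1.960 + 1.282)² / 0.56² = 21.01 / 0.3136 = 67.0, rounded up to 68. The noncentral t calculation also gives 68, with power 0.900. The figure reproduces, and nothing below touches it. The plan gives no size for the per-protocol set.

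**2. Who leaves the T2 comparison.**

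| Pattern | Set as written | Set using events up to T2 |
|---|---|---|
| T2 score, no psychotherapy by T2, start between T2 and T3 | out | in |
| T2 score, no psychotherapy by T2, T3 missed | out | in |
| T2 score, psychotherapy before T2 | out | out |
| No T2 score | out | out |

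The first two rows are the loss. Cooperating clinics have waits of at least two months, about 8.7 weeks, and T2 is at seven weeks. Some of the wait passes before randomisation, so some starts before T2 are possible. The Discussion nevertheless expects starts between T2 and T3.

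**3. Size of the one-arm module selection if there is no true effect.** Let latent adherence be standard normal, let the top share p complete five modules, and let c be its correlation with improvement. The intervention mean then shifts by c·φ(z_p)/p.

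- p = 0.6: φ(0.253)/0.6 = 0.386/0.6 = 0.644. With c = 0.2 the shift is 0.129 SD; with c = 0.3 it is 0.193 SD. These are 23% and 34% of 0.56.
- p = 0.7: φ(0.524)/0.7 = 0.348/0.7 = 0.497, giving 0.10 to 0.15 SD.

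Both p and c are assumptions; the documents give neither.

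**4. Direction.** This was simulated under no true effect, with a standard normal T2 score, logistic selection and one million per arm. Positive values favour the intervention. Odds ratios (OR) are per SD of T2 score, and all rates are assumed.

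| Selection | Bias at T2 (SD) |
|---|---|
| Modules only, completers better, 80% to 50% completing, OR 1.25 to 2 | +0.04 to +0.31 |
| Modules only, early improvers stop, 60% completing, OR 1.25 to 2 | −0.09 to −0.25 |
| Start rule only, same rate (20% or 40%) in both arms, OR 1.5 | about 0.00 |
| Start rule only, worse-off start more (OR 1.5), 20% intervention / 40% control | −0.08 |
| As above, 10% / 40% | −0.12 |
| As above, 40% / 20% | +0.08 |
| Combined: 60% completers (OR 1.5), 30% starts in both arms (OR 1.5), 75% with all assessments (OR 1.25) | +0.14 |
| Combined: 80% completers (OR 1.25), starts 20% / 45% (OR 2), 75% with all assessments (OR 1.25) | −0.11 |

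**5. Effect of the change.** Assume 5% start psychotherapy by T2 (OR 1.5), 80% give a T2 score (OR 1.25), and selection is the same in both arms. A T2 set built on events up to T2 without the module rule has bias of about 0.00. Keeping the module rule (60%, OR 1.5) leaves +0.15 SD. In that scenario the module rule causes nearly all of the bias; the separate T2 set mainly recovers data and removes the dependence on later events.

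**The case against.** The best defence is that little depends on this analysis. Intention to treat is the main analysis, the sample size is based on it, and the per-protocol analysis is already called additional. All of that stands.

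The protocol also says that waits depend on clinic capacity, and randomisation is stratified by clinic. If capacity alone drives psychotherapy starts, exclusions should be roughly balanced and the start rule nearly neutral, as the equal-rate row shows. That stands too, but the rule would still throw away good T2 scores, and missing T3 is not a matter of clinic capacity. The effect-size sentence is not expressly tied to the per-protocol set. Even so, a group-by-time model fitted in that set yields a T2 contrast with the same selection.

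It could be said that time-specific sets belong in an analysis plan that is not shown. But the article does not leave the rule open. It states one, and repeats its psychotherapy condition.

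Several stronger readings are tempting, and the documents do not support them:

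- *The set favours the intervention.* The sign depends on completion and start rates that are not given.
- *The set will shrink to about 16 versus 27.* That needs 50% starts, 80% with all assessments and 60% completers (68 × 0.5 × 0.8 × 0.6 = 16.3; 68 × 0.5 × 0.8 = 27.2). The mean wait of 4.5 months in Background is a German average, not a figure for these clinics. With 30% starts and 75% with all assessments the simulation leaves about 22 versus 36.
- *A control adherence criterion was forgotten.* None is possible by design.
- *A complier-average effect should replace the module rule.* With receipt defined as five modules, it requires that assignment does nothing for people who complete fewer. They still receive content, e-coach feedback, a mood diary and optional text messages, so the restriction is doubtful.

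**Conclusion.** The point holds for the additional analysis only. As written, a T2 per-protocol comparison discards valid scores obtained before psychotherapy because of later events, and it compares self-selected completers with controls who cannot be selected in the same way. The result is biased in an unknown direction. A bias towards the intervention is plausible if completers have the better prognosis: about 0.13 to 0.19 SD at 60% completion and a correlation of 0.2 to 0.3. The opposite sign arises if early improvers stop, or if worse-off controls start psychotherapy more often. All these sizes rest on assumed rates and serve as illustration, not forecast. The change is worth making because the protocol presents the analysis as a safeguard and the correction uses data already collected.

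**What to change.** Define the per-protocol set separately for each time point in Effectiveness analyses, and bring the Discussion into line:

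- **T2 set:** a T2 score and no psychotherapy session before the T2 date, taken from the first-appointment date, with no condition on later events.
- **T3 set:** the corresponding rule up to T3.
- **Modules:** report each result with and without the five-module restriction, and state that the restricted comparison is non-randomised and descriptive.
- **Rationale:** remove the claim in the Discussion that the per-protocol analysis serves data quality.
- **Optional:** a complier-average estimate as a sensitivity analysis, with its exclusion restriction stated. It should not replace the above.

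The cost is some redrafting and slightly more analysis. No new data are needed, and the T2 set keeps at least as many participants as the present one. The sets remain selected after randomisation, so the near-zero bias shown for the T2 set without the module rule holds only if selection up to T2 is alike in both arms.
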